## Abstract

*Background*: Young children are prone to low levels of physical activity in childcare. This environment, inclusive of equipment, policies, and staff, has been identified as influencing young children’s activity behaviours. To date, no study has examined the feasibility and effectiveness of such policies in Canadian childcare centres, while the provision of physical activity policies in other countries has shown some promise for improving the activity levels of young children. As such, the primary objective of the Childcare PhysicaL ActivitY (PLAY) Policy study is to examine the feasibility of an evidence-based, stakeholder-informed, written physical activity and sedentary time policy for centre-based childcare (i.e., at the institutional level). The secondary objectives are to examine the impact of policy implementation on the physical activity levels and sedentary time of young children, subsequent environmental changes in childcare centres, and childcare providers’ self-efficacy to implement a physical activity policy. This study will examine both policy implementation and individual (behavioural) outcomes. *Methods/Design*: The Childcare PLAY Policy study, a pilot, cluster-randomized controlled trial, involves the random allocation of childcare centres to either the experimental (*n* = 4) or control (*n* = 4) group. Childcare centres in the experimental group will adopt a written physical activity policy for eight weeks (at which time they will be asked to stop enforcing the policy). Physical activity levels and sedentary time in childcare will be assessed via ActiGraph^™^ accelerometers with measurements at baseline (i.e., week 0), mid-intervention (i.e., week 4), immediately post-intervention (i.e., week 9), and at six-month follow-up. Policy implementation and feasibility will be assessed using surveys and interviews with childcare staff. The Environment and Policy Assessment and Observation Self-Report tool will capture potential changes to the childcare setting. Finally, childcare providers’ self-efficacy will be captured via a study-specific questionnaire. A nested evaluation of the impact of policy implementation on young children’s physical activity levels will be completed. A linear mixed effects models will be used to assess intervention effects on the primary and secondary outcomes. Descriptive statistics and thematic analysis will be employed to assess the feasibility of policy implementation. *Discussion*: The Childcare PLAY Policy study aims to address the low levels of physical activity and high sedentary time observed in childcare centres by providing direction to childcare staff via a written set of evidence-informed standards to encourage young children’s activity and reduce sedentary time. The findings of this work will highlight specific aspects of the policy that worked and will inform modifications that may be needed to enhance scalability. Policy-based approaches to increasing physical activity affordances in childcare may inform future regulations and programming within this environment.

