The primary aim of the eight-week Childcare PLAY Policy study is to evaluate the feasibility of an evidence-based, stakeholder-informed, written physical activity and sedentary time policy in childcare centres. For the purpose of this study, feasible refers to the intervention being implemented as intended and well received by childcare providers. Specific objectives include determining whether the policy was effective at: (i) increasing young children’s (i.e., toddlers and preschoolers, age 18 months–4 years) physical activity (i.e., MVPA and total physical activity (TPA)); (ii) reducing young children’s sedentary time; (iii) producing a feasible and appropriate policy for use in the childcare setting; (iv) increasing childcare providers’ self-efficacy for facilitating young children’s physical activity during childcare; and (v) producing environmental changes in support of physical activity in childcare. Because the implementation of a policy may influence other aspects of the childcare, an environmental assessment will also be conducted. This pilot study will evaluate the feasibility and effectiveness of policy implementation within individual childcare centres, and it will afford the opportunity to modify the policy prior to examining its effectiveness in a larger, more diverse sample.

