
Policy Adherence Log (Childcare Providers). A log will be completed by childcare providers three times per week (i.e., Monday, Wednesday, and Friday) to monitor adherence to each statement of the policy during the eight-week intervention period. Childcare providers will check “yes” to indicate that they adhered to the policy statement, “part” to indicate that they only partially followed the policy item, and “no” to indicate that the policy statement was not followed on that particular day. Reasons the policy was not followed will also be indicated from a list of options (i.e., weather, ratios, no space, behaviour, other).

Self-Efficacy (Childcare Providers). To gauge potential changes in childcare providers’ self-efficacy to provide physical activity opportunities and overcome related barriers, a 40-item instrument was developed for the purpose of the study, which will be administered twice at baseline (to assess test, re-test reliability) and at all subsequent time points. Childcare providers will rate their confidence to each item on a scale from 0 (I am not at all confident) to 10 (I am highly confident) in line with the construction of self-efficacy scales (e.g., task and barrier) [38].

Program Evaluation Survey (Childcare Providers). Childcare providers from the experimental condition will complete a survey (Appendix C) at post-intervention to gather information to evaluate implementation of the policy. Specifically, their initial willingness to participate (one item), preparedness (one item), and the feasibility or ease of policy implementation (18 items), will be rated on a scale from 1 (strongly disagree) to 5 (strongly agree). Future implementation will be assessed via 17 items rated from 1 (not at all likely) to 5 (extremely likely), and communication (four items) will be rated from 1 (not at all effective) to 5 (extremely effective). Nine open-ended response questions will capture aspects of the policy that the childcare providers liked the most, those that they found to be most/least important, challenges encountered, solutions used, any modifications made, the noted success of modifications, and their overall experience with policy implementation. The tool was created for the purposes of this study.

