### 2.8. Analysis

All data will be entered, verified, and stored in our lab. Baseline characteristics of the children and the childcare centres will be summarized descriptively; participant characteristics for those who complete the study and those who drop out will be explored. All statistical analyses will be performed in R [31], using the lme4 [40] and lmerTest packages [41].

Implementation Log. Frequencies and percentage scores will be calculated to reflect adherence to policy statements and reasons that compliance was not attained will be reported descriptively.

Program Evaluation Survey and Interviews. Means and standard deviations of survey item ratings will be provided. Responses to open-ended program evaluation survey and interview questions will be analyzed using thematic content analysis [42] using QSR NVivo.

Physical Activity. Children’s physical activity data will be analyzed using a series of linear mixed effects models for each of the three outcome variables (i.e., TPA, MVPA, and sedentary time). Group (experimental versus control) and time (baseline, mid-intervention, post-intervention, and six-months post-intervention) will be modelled as a fixed effect, and will be evaluated using *t*-tests, with a Satterthwaite approximation determining degrees of freedom. Descriptive survey data will be analyzed using frequencies, *t*-tests, and chi-square tests.

Childcare Providers’ Self-Efficacy. Descriptive statistics will be reported to indicate changes in childcare providers’ self-efficacy specific to implementing physical activity in childcare. Classical test theory will be used to assess internal consistency of the scales, exploratory factor analysis will be used to assess the factorial validity of the measured constructs, and item response theory will be used to explore the item and scale characteristics of the measurements used to assess the two polytomous constructs in this study (i.e., task and barrier self-efficacy). Factor analysis and classical test theory analyses will be undertaken within the psych package [43] and the ltm package [44] will be used for the item response theory analyses.

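### Provider self-efficacy is an effectiveness objective measured in both arms, but section 2.8 plans only descriptive change and no between-arm estimate

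*Protocol article*

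**What the plan says.** The Abstract lists "childcare providers’ self-efficacy to implement a physical activity policy" among the subjects of the secondary objectives. For analysis it states: "A linear mixed effects models will be used to assess intervention effects on the primary and secondary outcomes".

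The Background is framed in terms of effect: "Specific objectives include determining whether the policy was effective at" five things, of which (iv) is raising providers' self-efficacy. The Hypothesis section expects a rise among providers in the experimental group.

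Under Self-Efficacy, section 2.7 says that "a 40-item instrument was developed for the purpose of the study", rated 0 to 10, given twice at baseline for test-retest reliability and again at every later time point. Table 2 marks it in both conditions at baseline, week 4, week 9 and six months.

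In section 2.8, the paragraph on this outcome opens "Descriptive statistics will be reported to indicate changes in childcare" providers' self-efficacy. It names no comparison of groups and no model. It then turns to the instrument itself: internal consistency, exploratory factor analysis, and "item response theory will be used to explore the item and scale characteristics of the measurements" for the task and barrier constructs.

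**The concern.** The objective asks whether the policy changed self-efficacy. The design supplies what is needed to answer that: randomised centres, a control arm and repeated measurement in both arms. The analysis section does not use the control arm for this outcome. Scores on a confidence questionnaire can drift when the same people answer it repeatedly, with or without a policy. A rise in the experimental arm alone therefore cannot be attributed to the policy, and a reader of the Abstract would expect a modelled intervention effect that section 2.8 does not plan.

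The same paragraph commits to demanding measurement models for a new instrument, with no statement of how many providers will complete it. The risk is that unstable factor or item-response results are reported as evidence about the scale.

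**Working it through.** **1. Does each effectiveness outcome get a between-arm analysis?** Comparing the Background objectives with section 2.8:

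- (i) and (ii), children's activity and sedentary time: linear mixed effects models with group and time.
- (iii), a feasible and appropriate policy: adherence frequencies, survey summaries and thematic analysis. This is not an outcome for between-arm comparison.
- (iv), provider self-efficacy: descriptive statistics of change.
- (v), childcare environment: logistic regression with group and time.

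Of the four quantitative effectiveness outcomes (i, ii, iv, v), only self-efficacy has no model with group and time.

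**2. How often is the questionnaire repeated?** Two baseline administrations plus week 4, week 9 and six months: 2 + 3 = 5. Change from baseline within one arm mixes any policy effect with the effect of repetition and anything else that alters over the period. The difference in change between arms removes what the two arms share, and that contrast is not planned.

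**3. Can the provider sample carry the measurement models?** The article gives no provider number, so there is no stated figure to reproduce. The sample size calculation in section 2.3 concerns children only. Inputs from the document: 8 centres (section 2.4), full-time toddler/preschool providers only (Table 1), 40 items scored 0 to 10 (section 2.7), hence 11 categories if whole numbers are used. Assumption: 3 to 15 eligible providers per centre.

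- Providers: 8 x 3 = 24 to 8 x 15 = 120.
- Providers per item: 24/40 = 0.6 to 120/40 = 3.0.
- Average responses per category per item: 24/11 = 2.2 to 120/11 = 10.9.
- If the task and barrier scales have 20 items each (assumption) and are analysed separately, providers per item: 24/20 = 1.2 to 120/20 = 6.0.

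For illustration only, since the article names no item-response model: an unconstrained graded response model has one slope and 10 thresholds per item, so 40 x 11 = 440 parameters for all items, or 20 x 11 = 220 for one 20-item scale. One provider per parameter would need 440/8 = 55 or 220/8 = 27.5 providers per centre. The recruitment target is 218/8 = 27.25 children per centre, so neither is plausible. Pooling the five administrations adds repeated answers from the same people, not independent respondents.

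**The case against.** **The Abstract may be a loose summary.** Its mixed-model sentence follows one on the nested evaluation of children's activity and may describe only that. Read literally it would also cover the primary feasibility outcome, which the next sentence gives to descriptive and thematic analysis. This is fair: the sentence does not prove that a model for self-efficacy was intended. The gap between objective (iv) and section 2.8 remains on either reading.

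**Descriptives could be given by arm.** Section 2.8 does not exclude this, so it would be too strong to infer that objective (iv) cannot be informed at all. Summaries by arm and time would bear on it, but would give neither an estimate of the difference nor an interval that respects clustering. The sentence in section 2.8 on t-tests and chi-square tests does not fill the gap: it stands in the Physical Activity paragraph, concerns descriptive survey data, and ordinary t-tests ignore centre and repeated measurement.

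**Descriptive reporting suits a pilot.** With four centres per arm and feasibility as the primary aim, this is defensible. The objective and the Abstract should then say so.

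**The measurement point can be overstated.** A reader might infer that the sample cannot support the models, that factoring must break down at 40 or fewer providers, or that the results would redefine the outcome score. The document does not support these. The provider number is unknown. A singular correlation matrix at 40 or fewer arises only if all 40 items are factored together; for 20-item scales the limit is 20, below the assumed minimum of 24. No extraction method is named. Task and barrier are fixed in advance, and no rescoring is planned.

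**Conclusion.** The main point holds on the text. Objective (iv) is worded as an effect of the policy, the controlled data will exist, and section 2.8 plans no between-arm estimate, unlike the other quantitative effectiveness outcomes. It should be corrected, but it concerns a secondary outcome and does not touch the feasibility aim. No size can be put on the effect or its precision, because the article gives no provider number, standard deviation, intra-cluster correlation or target difference for this scale.

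The secondary point is a judgement resting on the assumed 3 to 15 providers per centre. Across that range, 0.6 to 3 providers per item makes stable factor or item-response results very unlikely. It does not show that the analyses are impossible.

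**What to change.** In section 2.8, state a linear mixed model for each of the task and barrier scores: fixed effects for group, time and group x time, with baseline as one of the four time levels, and random intercepts for provider and centre. Say which of the two baseline administrations serves as baseline, and which time-point contrast answers objective (iv); week 9 is the natural choice. Report the between-arm difference with 95% CI and label it exploratory, given eight centres. If the analysis is to stay descriptive, reword objective (iv) as descriptive and limit the Abstract's mixed-model sentence to the children's outcomes.

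State the expected number of providers. Keep internal consistency and test-retest reliability, both already planned. Label the factor and item-response analyses exploratory, or defer them to the larger study that the Background foresees.

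The cost is some wording and one more model per score on data already being collected. The interval will be wide. Random intercepts alone also do not let centres differ in their change over time, so the interval may still be somewhat too narrow, which is a further reason for the exploratory label. Part of the psychometric work may be postponed.

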## 3. Discussion

Evidence-informed approaches to supporting and encouraging appropriate physical activity participation (and limiting periods of sedentary time) during childcare hours are warranted. A substantial body of evidence suggests that childcare programming and the environment strongly influence young children’s physical activity levels [45,46]. In fact, childcare centres influence preschoolers’ activity levels more than individual-level factors, such as age, sex, and ethnicity [47]. Despite recognition that childcare venues are an ideal setting to intervene and the call for institutional-level physical activity policies in childcare centres [23], the feasibility and effectiveness of a physical activity and sedentary time policy, specifically within the Canadian context, is lacking. A written physical activity and sedentary time policy may help to promote providers’ self-efficacy by providing specific direction in terms of how to best engage children in daily activity. Moreover, creating and implementing such policies would ensure that all children attending these facilities are afforded the opportunity to be physically active, and offer a greater chance of meeting the daily recommendation. Young children spend two-thirds of their day in childcare, suggesting that two-thirds of the daily movement requirement (180 mins of TPA; 60 mins of MVPA), may be achieved during childcare hours (120 mins of TPA; 40 mins of MVPA). Implementation of an activity-focused childcare policy provides an opportunity to “level the playing field” in terms of ensuring consistent affordances within this setting and represents a promising population-based approach (with access to over 50% of this Canadian cohort) for supporting active behaviours.

While Alberta has demonstrated that new accreditation standards show promise in improving activity levels among young children [26], this research will be the first to explore the feasibility and effectiveness of an institutional-level written childcare policy intervention as a mechanism to support improved physical activity levels (and minimize sedentary time) among young children in Ontario. By providing specific, evidence-informed guidance that offers strategies for achieving success at increasing physical activity and reducing sedentary time, childcare providers will be in a better position to ensure their programming is in line with Canadian recommendations [48]. Moreover, this study will offer an understanding of the uptake and receptivity of childcare centres to implementing such a policy, and feasibility and the burden of doing so. If effective, and appropriate to implement, the findings from the Childcare PLAY Policy study have the potential to guide institutional-level policies (short-term) and higher-level regulatory amendments to provincial standards (long-term). The effectiveness of the intervention rests in the creation of a physical activity policy that childcare providers believe is important and feasible to implement and aligns with their current curriculum and pedagogy. The results of the Childcare PLAY Policy will be shared with participants and childcare professionals and stakeholders via publications, infographics, and presentations.

## Figures and Tables

**Table 1 ijerph-16-04400-t001:** Inclusion and exclusion criteria for the Childcare PLAY Policy study.

Participant	Inclusion Criteria	Exclusion Criteria
Childcare Centres	Centre-based facility in London, Canada At least one toddler or preschool classroom Childcare providers willing to participate ≥8 children who received parental consent English-speaking centre Does not currently have an institutional-level PA policy	Home-based childcare or after-school care only Not located in London, Canada or surrounding area Do not have a toddler or preschool-age classroom Childcare providers not willing to participate <8 children with parental consent Not an English-speaking facility Already has an established institutional-level PA policy
Childcare Providers	Full-time childcare provider in a toddler/preschool classroom Speaks and writes English	Not full-time Not a childcare provider in a toddler/preschool classroom Does not speak/write in English
Toddler/ Preschool Participants	Enrolled at a participating childcare centre 18 months–4 years Expected to remain at centre for next eight months Enrolled in a toddler/preschool classroom Parent/guardian speaks and understands English Has parental/guardian consent	Not enrolled at a participating childcare centre Not 18 months–4 years Not expected to remain in care for next eight months Not enrolled in a toddler/preschool classroom Parent/guardian does not read/write in English No parental/guardian consent

*Note.* PA = physical activity.

**Table 2 ijerph-16-04400-t002:** Outcome assessments for the Childcare PLAY Policy study.

Participant/Tool		Control Condition				Experimental Condition			
		Baseline (week 0)	Mid-Int (week 4)	Post-Int (week 9)	6M	Baseline (week 0)	Mid-Int (week 4)	Post-Int (week 9)	6M
Toddlers/ Preschoolers	Parent/Guardian Demographic Q	x				x			
	Physical Activity/ Sedentary Time (ActiGraph™ data)	x	x	x	x	x	x	x	x
	Anthropometrics	x				x			
Childcare Providers	Demographic Q	x				x			
	Policy Adherence Log (week 1–8) *		x				x		
	Program Evaluation Survey							x	
	Interview							x	
	EPAO-SR General	x	x	x	x	x	x	x	x
	EPAO-SR Today	x	x	x	x	x	x	x	x
	Self-Efficacy Q	x	x	x	x	x	x	x	x
Directors	Director General EPAO-SR	x				x			

*Note*. Mid-Int = mid-intervention, Post-Int = post-intervention, M = month, Q = questionnaire, EPAO-SR = Environment and Policy Assessment and Observation Tool—Self-Report Tool. * Policy Adherence Log was maintained for the duration of the eight-week intervention, but not at baseline or post-intervention/follow-up measurements.

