### 2.6. Development and Implementation of the Childcare PLAY Policy

To promote policy engagement, buy-in, and suitability, the policy was developed by our research team in collaboration with an advisory committee that included childcare organizations and centre administrators, childcare providers, municipal childcare stakeholders, and a policy expert. The policy was created following a review of relevant literature on the importance of outdoor play [32], unstructured activity [29,33], and informed by the Canadian 24-Hour Movement Guidelines for the Early Years (0–4 years; [3]). The current version of the policy includes eight statements that are designed to provide specific recommendations for time in energetic play (i.e., minimum of 40 min/day), outdoor time (i.e., 120 min/day), and suggests short (i.e., 15–30 min), frequent (i.e., 3–4 times/day) outdoor periods during childcare hours. It requires that children be exposed to a variety of indoor and outdoor physical activities to promote physical literacy and recommends appropriate role modelling of screen-based technology, with no screen time permitted for children during childcare hours. Sustained sedentary time is recommended to be disrupted and replaced with physical activity. See Appendix A for the Childcare PLAY policy.

Experimental Condition. For eight weeks, childcare providers in the experimental centres will be asked to implement the written policy that outlines optimal physical activity daily affordances and sedentary time recommendations during childcare. Prior to the eight-week intervention period, childcare providers will participate in a training session, led by the project coordinator. The session will last approximately an hour in length, which will detail the characteristics of the study design, review the policy, its implementation, and study tools (e.g., accelerometer logs).

Control Condition. Childcare centres randomly assigned to the control group will be asked to continue their typical daily curriculum for the duration of the eight-week intervention and follow-up period. Upon completion of the study, all centres allocated to this group may opt to receive a copy of the written physical activity policy and the training regarding its implementation.

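### Table 2 schedules the Policy Adherence Log in the control arm, which conflicts with a control condition that withholds the policy until the study ends

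*Protocol article*

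**What the plan says.** Table 2 lists the log as "Policy Adherence Log (week 1–8") and marks it once in the control columns and once in the experimental columns, both under mid-intervention. The note to the table explains the timing but names no arm: "Policy Adherence Log was maintained for the duration of the eight-week intervention, but not at baseline or post-intervention/follow-up measurements".

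Section 2.7 gives the frequency, "A log will be completed by childcare providers three times per week (i.e., Monday, Wednesday, and Friday"), and the purpose, "to monitor adherence to each statement of the policy during the eight-week intervention period". Providers record full, partial or no adherence to each statement and choose reasons for any failure from a list. No arm is named here either. Section 2.6 fixes the content to be rated: "The current version of the policy includes eight statements".

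The control condition is also in section 2.6. Control centres "will be asked to continue their typical daily curriculum for the duration of the eight-week intervention and follow-up period". As for access to the policy: "Upon completion of the study, all centres allocated to this group may opt to receive a copy of the written physical activity policy".

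**The concern.** A control provider cannot rate adherence to each statement of a policy without being told what the statements are. The intervention consists of a written document and one training session of about an hour, so the statements are a large part of its active content: the energetic-play and outdoor-time targets, the limits on screens, and the breaking up of sedentary time. A form that repeats them several times a week and asks why each was not met also prompts self-monitoring.

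The comparisons at stake are the accelerometer outcomes and provider self-efficacy, both measured in both arms. The hypothesis expects no change in control children, and the Discussion suggests that a written policy may raise self-efficacy by giving specific direction. Exposing controls to that direction would work against the contrast the trial is meant to estimate.

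A smaller issue is that section 2.8 plans frequencies and percentages of adherence without naming an arm. Pooling entries from centres that have no policy would make those percentages hard to interpret.

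**Working it through.** The plan states no figure on this point, so the check is a comparison of the relevant places and a count of scheduled exposure.

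**1. Is the control mark really in the table?** The log row has two marks, which fall under Control Mid-Int and Experimental Mid-Int. In the same table the Program Evaluation Survey and Interview rows have a single mark each, under Experimental Post-Int, as section 2.7 says they should. The columns are therefore aligned, and the control mark is not a shift caused by text extraction.

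**2. Does other text remove it?**

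| Place | Respondents | Arm named? |
|---|---|---|
| Table 2, log row | Childcare providers | Both arms marked |
| Note to Table 2 | Not stated | No |
| Section 2.7, log | Childcare providers | No |
| Section 2.7, survey | Childcare providers | Experimental only |
| Section 2.7, interviews | Childcare providers | Experimental only |
| Section 2.8, log analysis | Not stated | No |

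The survey and the interviews are expressly limited to the experimental arm, and the log is not. Nothing in the text overrides the control mark.

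**3. Is it compatible with the control condition?** Under section 2.6, controls continue as usual through intervention and follow-up and may see the policy only afterwards. Table 1 also excludes centres that already have an institutional physical activity policy, so a control centre has no such policy of its own to rate. Table 2 and section 2.6 are incompatible unless the control log differs from the one in section 2.7, and no such version is described.

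**4. Scheduled exposure if followed as written.**
- Log days: 3 per week x 8 weeks = 24.
- Statement ratings: 24 log days x 8 statements = 192.

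These are upper limits for one provider, since section 2.7 does not say that every provider completes every log. With the log limited to the experimental arm, control exposure by this route is 0.

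**5. Direction and size of any bias.** If controls took up a fraction c of the effect d, the observed contrast would be (1 − c) x d, which is smaller than d for any c above 0. The documents give no value for c and nothing from which to derive one. The direction follows; the size does not.

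**The case against.** The strongest reply is that the control mark is a slip. Section 2.7 speaks of adhering to the policy and of reasons it was not followed, which fits only staff who have a policy, and section 2.6 describes training on it only for experimental centres. If so, no control provider would see the log and nothing would be contaminated. This is plausible. It still leaves a published schedule that tells centres to do something the control condition rules out. Deliberate use in both arms cannot be excluded, because the log, unlike the survey and the interviews, is not limited to one arm.

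A second reply is that a control log could be useful: it would record policy-like practice in usual care and so the contrast actually achieved. That stands in part. The EPAO-SR forms are less frequent, with General given once in each data-collection week and Today on one chosen day per time point. A control log would nevertheless have to avoid disclosing the statements, and the plan does not say that it does.

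Three stronger readings are tempting but not supported:
- A reader might infer that contamination is certain. The log form is not among the appendices, so what control staff would see is unknown.
- A reader might want to express the harm as lost power. That needs an uptake fraction, and any value would be invented.
- A reader might infer that the primary feasibility aim is compromised. Feasibility is described from the log, the survey and the interviews. The last two are experimental-only, and control log entries could be reported separately.

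**Conclusion.** The inconsistency is real. Table 2 gives control providers the Policy Adherence Log, section 2.7 and the table note do not take it away, and section 2.6 withholds the policy from them until the study is over.

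The consequence is conditional. If the schedule is followed as written and the log shows the policy statements, control providers meet the intervention content on up to 24 log days. The TPA, MVPA, sedentary-time and self-efficacy comparisons would then tend to be biased toward no difference, by an amount that cannot be calculated from the documents. If the mark is an error, the defect is confined to the table. Either way the places need to be reconciled, and the correction is worth making because it is cheap and removes an avoidable threat to the between-arm comparison.

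**What to change.** 1. Remove the control-arm mark for the Policy Adherence Log in Table 2.
2. State in section 2.7 that only providers in experimental centres complete the log.
3. State in section 2.8 that adherence frequencies and percentages are calculated from the experimental arm only.
4. Describe control practice from EPAO-SR General and EPAO-SR Today, which Table 2 already schedules in both arms on all four occasions.

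If a control log is intended, say so instead, and state that it is a neutral practice log that does not disclose the policy statements.

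The cost is one table cell and two sentences, with no change to sample size. The small downside is that the EPAO-SR gives less frequent information on control practice than a log kept three times a week.
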